## INTRODUCTION

1

Epilepsy, the tendency to recurrent unprovoked seizures,^1^ is a chronic neurological disorder that presents across the lifespan and affects approximately 2% of the sub‐Saharan African population.^2^ Although epilepsy is usually treatable with one or more antiseizure medications (ASMs), a significant number of people with epilepsy (PWE) in low‐resource settings do not have access to or do not regularly take ASMs.^2^ Multiple organizations and investigators have noted the *epilepsy treatment gap*—defined as the difference between the number of PWE who have active epilepsy treated with ASMs versus not or the proportion of people that should be treated for epilepsy yet are not—but few studies provide an evidence base on how to change the current situation.^3^, ^4^, ^5^, ^6^ Most recently, the World Health Assembly adopted the *Intersectoral Global Action Plan on Epilepsy and Other Neurological Disorders* (“Draft Intersectoral global action plan on epilepsy and other neurological disorders 2022–2031,”^7^). This includes targets to treat more people with neurological disorders with essential medicines including ASMs for PWE.

Cascades of care are being developed to assess the delivery of care for noncommunicable diseases, similar to the approach seen in HIV/AIDS.^8^ In a cascade, specific targets are identified including: (1) ensuring >90% of PWE are aware of the diagnosis as a brain disorder, (2) retaining >90% of PWE in epilepsy care, (3) ensuring >80% of PWE take quality, appropriate chosen and dosed ASMs, and (4) ensuring seizure freedom in 70% of people treated.^9^ Of these, seizure freedom (step four) is the outcome most valued by PWE and is associated with a self‐reported quality of life equivalent to people without epilepsy. Given the high efficacy of ASMs, access to ASMs would lead to seizure freedom in a majority of PWE.

Access to ASMs remains a challenge to seizure prevention and epilepsy treatment in low‐resource settings. Epilepsy care in the Republic of Guinea, a low‐income country in Western Sub‐Saharan Africa with a 2020 gross national income of 1020 USD per capita,^10^ reflects a low‐functioning health system with few epilepsy‐trained clinicians, and high volumes of patients. Guinea has few health facilities and a nearly completely privatized healthcare system, necessitating costs to be paid “out of pocket.” PWE often go without ASMs due to multiple factors at the level of the patient, provider, and health system.

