### Objectives

1.2

The primary objective is to implement and test a novel strategy to improve outcomes across the epilepsy care cascade marked by (1) retention in epilepsy care, (2) adherence to ASMs, and (3) seizure reduction with the measured goal of seizure freedom.

The first aim is to compare free ASMs vs. conditional cash using the epilepsy cascade of care. We hypothesize that the provision of free medication versus conditional cash will lead to (1) similar retention in epilepsy care—90% of PWE—at 360 days (Hypothesis 1a), (2) 80% of PWE regularly taking ASMs at 360 days (Hypothesis 1b), and (3) 65% of PWE achieving seizure freedom 360 days postenrollment (Hypothesis 1c).

The secondary aim is to detail facilitators and barriers to free medication versus conditional cash to improve seizure freedom among PWE. We hypothesize that barriers and facilitators to the uptake of each intervention strategy can be learned through careful, structured documentation by healthcare workers during study visits using an investigator‐designed written intake form as well as free‐text responses, serving as foundational information for a future larger‐scale implementation study in low‐resource populations.

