For Hypothesis 1b, we will use a one‐sample proportion test to test the null hypothesis that the percentage of PWE regularly taking ASMs at 12 months in the conditional cash arm is less than or equal to 85%, and we will use a two‐sample proportion test for the null hypothesis that the percentage of PWE regularly taking ASMs in the conditional cash arm is less than or equal to the percentage of PWE regularly taking ASMs in the free medication arm. For Hypothesis 1c, we will use a one‐sample proportion test to test the null hypothesis that the percentage of PWE with seizure freedom at 12 months in the conditional cash arm is less than or equal to 65%, and we will use a two‐sample proportion test for the null hypothesis that the percentage of seizure freedom in the conditional cash arm is less than or equal to the percentage of seizure freedom in the free medication arm.

To leverage the longitudinal observations collected during follow‐up visits at 90, 180, 270, and 360 days, we will use a generalized linear mixed effects model which allows us to study the association between multiple baseline variables (e.g., including the intervention options, education level, medication status, ASM type, distance to the study clinics) while accounting for the correlation between longitudinal observations.

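### Hypothesis 1b is set at 80% but tested against 85%, and the 1b and 1c nulls, read literally, are margin-free superiority tests with little chance of success at the hypothesised rates

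*Protocol article*

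**What the plan says.** Section 1.2 (Objectives) gives one figure per outcome for free medication versus conditional cash: "80% of PWE regularly taking ASMs at 360 days (Hypothesis 1b") and "65% of PWE achieving seizure freedom 360 days postenrollment (Hypothesis 1c"). The Introduction lists the matching cascade target as "ensuring >80% of PWE take quality, appropriate chosen and dosed ASMs".

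Section 6 (Statistical Methods) then sets four nulls for these two hypotheses:

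- 1b, one sample: the percentage "regularly taking ASMs at 12 months in the conditional cash arm is less than or equal to 85" per cent.
- 1b, two samples: the percentage "in the conditional cash arm is less than or equal to the percentage of PWE regularly taking ASMs in the free medication arm".
- 1c, one sample: the "percentage of PWE with seizure freedom at 12 months in the conditional cash arm is less than or equal to 65" per cent.
- 1c, two samples: the cash-arm percentage "is less than or equal to the percentage of seizure freedom in the free medication arm".

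For Hypothesis 1a the same section names non-inferiority tests, with margins of 8.5% (one sample) and 12% (two samples). For 1b and 1c it gives no non-inferiority label, margin, alpha or power. The sample size is stated to rest on 1a alone. Table 2 lists seizure freedom as a secondary outcome and ASM adherence as an exploratory one.

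**The concern.** There are two separate problems.

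The first is a contradiction in a number. The figure of 85% appears nowhere else in the article as an adherence target. It cannot be 80% adjusted by a non-inferiority margin, because that would put the null below 80%, not above it. An analyst following section 6 and one following section 1.2 could reach opposite conclusions on 1b from the same data.

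The second is the match between hypothesis and test. Section 1.2 does not predict that cash will beat free medication on adherence or seizure freedom, yet the two-sample nulls are rejected only if cash is better. The one-sample null for 1c equals the hypothesised rate, and the one for 1b lies above it. If the trial turned out as hypothesised, the likely report would be four non-significant tests, which readers could take as evidence against 1b and 1c.

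**Working it through.** **Inputs.** 200 participants randomised 1:1, so 100 per arm (section 1.1). Hypothesised rates are 80% and 65% (section 1.2); null values are 85% and 65% (section 6). Alpha for 1b and 1c is not stated, so I use one-sided 0.05 and 0.025; the latter is the Bonferroni share of 0.05 over the two 1a tests. Using all 100 per arm is also an assumption.

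**The plan's own figures for 1a.** With one-sided 0.025 and 80% power, (1.960 + 0.842)² = 7.849.

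- One sample: n = 7.849 × 0.9 × 0.1 / 0.085² = 97.8, rounded up to 98.
- Two samples: n = 7.849 × 2 × 0.9 × 0.1 / 0.12² = 98.1, rounded up to 99 per arm.

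Both match section 6, so 1a was sized on non-inferiority at one-sided 0.025.

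**One-sample tests for 1b and 1c.** For an exact binomial test with n = 100, the critical value r is the smallest count with P(X ≥ r | null) ≤ alpha. The chance of success is P(X ≥ r | true rate).

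| Test | True rate | r at 0.05 | Success | r at 0.025 | Success |
|---|---|---|---|---|---|
| 1b against 85% | 80% | 92 | 0.09% | 93 | 0.03% |
| 1b against 80% | 80% | 87 | 4.7% | 89 | 1.3% |
| 1c against 65% | 65% | 74 | 3.5% | 75 | 2.1% |
| 1b against 85% | 90% | 92 | 32% | 93 | 21% |
| 1b against 80% | 90% | 87 | 88% | 89 | 70% |
| 1c against 65% | 75% | 74 | 64% | 75 | 55% |

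At one-sided 0.05, an observed 87 to 91 adherent of 100 passes against 80% and fails against 85%. A normal-approximation test shifts some of these figures (1b against 85%: 0.23% at 0.05; 1c: 5.6%) without changing the picture.

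**Two-sample tests.** One-sided pooled z-test, 100 per arm, full enumeration with equal true rates: 5.0% (2.6%) at 80% in both arms and 5.0% (2.5%) at 65% in both arms, for alpha 0.05 (0.025). This is alpha, as expected when the null is true.

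**True rates needed for 80% power, n = 100.** 1b against 85%: 93.6% at 0.05, 94.4% at 0.025. 1c against 65%: 77.1% and 78.0%.

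**Precision of the arm difference.** The 95% half-width is 1.96 × √(2p(1−p)/100). At p = 0.65 it is 1.96 × √0.00455 = 0.132; at p = 0.80 it is 1.96 × √0.0032 = 0.111.

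**Borrowing 1a's 12% margin, for illustration.** Power = Φ(0.12/√(2p(1−p)/100) − 1.96) at one-sided 0.025.

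- p = 0.80: Φ(2.121 − 1.960) = 56%; 80% power needs 175 per arm.
- p = 0.65: Φ(1.779 − 1.960) = 43%; 80% power needs 249 per arm.

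**The case against.** The conflict between 80% and 85% has no answer in the text. The second part does face a fair case.

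- **Equal arms are not stated.** A reader might infer that the objectives assert equal percentages in the two arms for 1b and 1c. Section 1.2 attaches the word for similarity to retention only. Equal rates are a natural reading of one figure per outcome, but still a reading.
- **The percentages may be floors.** The Introduction writes the retention and ASM targets as values to exceed, and section 6 expects cash-arm retention above its 90% figure. A floor is an ordinary one-sided null. On that reading the tests have some power, as the table shows for true rates of 90% and 75%. It is therefore too strong to infer that these tests cannot confirm the hypotheses they serve.
- **The framework is not certain.** The verbal one-sample null for 1a also omits its margin, although that test is called non-inferiority. Similar wording for 1b and 1c does not by itself prove a superiority framework. Still, the label and margins given for 1a are absent here, so superiority remains the more natural reading.
- **The consequences are limited.** These outcomes are secondary and exploratory, and section 6 also plans a longitudinal mixed model that includes the intervention and does not use these nulls. This stands and lowers the severity. Against it, section 1.2 places all three cascade outcomes in the primary objective.

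Using 100 analysed per arm is optimistic, given 90% hypothesised retention and no imputation (section 5.1). Fewer participants would make precision worse: with 90 per arm the half-width at 65% is 1.96 × √(0.455/90) = 0.139.

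**Conclusion.** The 1b threshold is wrong as written: section 6 contradicts section 1.2 and the Introduction, and the difference moves the success threshold by five participants in 100 at one-sided 0.05, or four at 0.025.

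Aligning the number alone does not settle the second problem. Taken literally, and with 80% and 65% reached in both arms, all four nulls are true, and success is a false positive at about alpha or far below it. That conclusion depends on the literal reading, an assumed alpha and 100 analysed per arm. It does not show that the tests are incapable of success, since a cash arm well above the benchmarks would have a reasonable chance on some of them. Nor does it touch the primary outcome or the sample size for 1a. The point should be fixed but is not critical to the trial.

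**What to change.** 1. Reconcile the 1b threshold across the Introduction, section 1.2 and section 6. Use the 80% of Hypothesis 1b unless the authors justify 85%.
2. Report 1b and 1c as the cash-arm proportion with its exact 95% confidence interval, set against 80% and 65%, and the arm difference with its 95% confidence interval.
3. State that these comparisons are not powered (half-width about 13 points at 65%), and that failing to reject a superiority null does not refute 1b or 1c.
4. If a non-inferiority claim is wanted for either outcome, justify and fix a margin before outcome data are seen, and acknowledge the low power that a margin of 1a's size would give.

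The design and sample size stay as they are. The cost is revised analysis wording and a more modest claim: 1b and 1c become estimates rather than tests of success. A move to non-inferiority would be a change of framework and should be declared as one.

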### Eligibility criteria

2.2

PWE will be screened in person and enrolled on a “first come, first served” basis. The goal is to enroll a person with active epilepsy. The person will have therefore experienced two or more recurrent, unprovoked seizures in the past year (inclusion criterion) and not have had any other diagnosis that can better explain the symptoms, as evaluated by the study neurologists (one Guinean and one U.S.). Specifically, patients with exclusively febrile seizures, pseudo‐seizures, and other movement disorders or episodic events that are not primary epilepsy are not eligible. The study will include a brain MRI such that secondary seizures from a space‐occupying lesion (secondary to tumor, stroke) can be detected and referred to usual care but not enrolled. Similarly, seizures that are provoked (e.g., alcohol withdrawal) will be queried through the intake forms and corroborated by physical examination and extant medical records.

Inclusion criteria are (1) resident of Guinea, 18 years or older, presenting to one of the study sites in Guinea; (2) able to provide informed consent or have a next of kin proxy provide informed consent when appropriate; (3) experienced two or more recurrent, unprovoked seizures in the past year; (4) able to provide a clinical history or have a next of kin provide it; (5) not taking a daily ASM for epilepsy for the past 30 days or more for any reason; (6) willing to have his/her data sent anonymously to the U.S. study site; and (7) anticipated to be able to return for follow‐up visits for 360 days.

Exclusion criteria are (1) any other diagnosis that can better explain the symptoms, making the diagnosis of primary, active epilepsy unlikely; (2) unable to undergo the study procedures; (3) age less than 18 years old due to the need to measure several self‐reported outcomes; (4) unable to provide informed consent (or have an appropriate proxy informed consent); (5) currently pregnant or lactating; (6) secondary seizures, for example, due to a condition that requires imminent treatment (e.g., malignancy, alcohol withdrawal); (7) critically ill; (8) exclusively pseudo‐seizures/nonepileptic behavioral events; (9) unwilling to take an ASMs for epilepsy; (10) already treated with ASMs for other purposes (e.g., mood, pain); (11) known to be unable to return for follow‐up visits.

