### Outcomes

3.3

The primary outcome of the study is adherence to neurology clinic appointments. This is defined as the number of appointments attended as scheduled and on time by the participant, as reported by the investigator.

Secondary outcomes are as follows:
Percent of PWE who achieve seizure freedom.Seizure frequency reduction: The percentage decrease in number of monthly seizures from baseline to the study endpoint of 360 days.

A complete list of outcomes can be found in Table 2.

**TABLE 2 epi412889-tbl-0002:** Primary, secondary, and exploratory outcomes of interest.

Outcome category	Outcome	Definition	Method of measuring
Primary	Adherence to Neurology Clinic Appointments	The number of appointments attended as scheduled and on time by the participant	Investigator reported
Secondary	Seizure freedom	% of PWE who achieve seizure freedom, or the ability to live without seizures of any type	Seizure diary counts
Secondary	Seizure frequency reduction	The percentage decrease in the number of monthly seizures from baseline to the study endpoint of 360 days	Seizure diary counts
Exploratory	Quality of life in epilepsy	A standardized scale and subjective report of physical, social, and psychological well‐being by a person with epilepsy	Patient/parent reported
Exploratory	Number of visits to traditional healers	Self‐reported number of visits to non‐allopathic providers for epilepsy management	Patient reported
Exploratory	Self‐reported adherence to ASMs	The number of pills left in the medication bottle, determined as a medication possession ratio	Investigator Counted
Exploratory	Stigma scale in epilepsy	A standardized scale and subjective report of stigma perceived by a person with epilepsy	Patient reported
Exploratory	Days attended at work or school	Self‐reported days attending school or work by a person with epilepsy of the past 90 days	Patient reported
Exploratory	Number of unintentional injuries due to seizures	Including burns, fractures, head injury, and related injuries in the past 90 days	Patient reported
Exploratory	Number of status epilepticus events	Reported by participant and family member in a log, articulating a seizure episode lasting >5 min	Patient reported

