### Participant timeline

3.4

The timeline of screening, enrolment, and interventions is provided in Table 3. The interventions will be provided at follow‐up visits taking place every 90 days. The baseline visit will include a neurologist's description of seizure history, including seizure semiology, epilepsy diagnosis, and etiology of epilepsy to the degree possible given resource limitations. Structured forms will be used. Several measures will be collected during follow‐up visits, including detailed seizure information, quality of life surveying, medication possession, stigma scale surveying using the Stigma Scale of Epilepsy (SSE),^26^ health visit history, school/work attendance, and injury surveying.

**TABLE 3 epi412889-tbl-0003:** Schedule of tests and events at each study visit.

	Screening	Baseline	90	180	270	360
Study visit		1	2	3	4	5
Informed consent	×					
Assess inclusion and exclusion criteria	×	×				
Medical history	×	×				×
Seizure diary		×	×	×	×	×
Concomitant medication history		×		×		×
Quality of Life in Epilepsy‐31 scale		×	×	×	×	×
Consumption and household assets module		×				×
Stigma Scale of Epilepsy		×	×	×	×	×
Medication possession ratio, as appropriate based on assigned arm			×	×	×	×
Health visit history (allopathic and traditional)		×	×	×	×	×
School/work attendance log		×	×	×	×	×
Injury survey		×	×	×	×	×
Status epilepticus query		×	×	×	×	×
Body weight, height, heart rate		×				×
Urine pregnancy test (for people of childbearing potential), *as needed	×	*	*	*	*	*
Clinical labs (including serum Na+, glucose), *as needed	*	×	*	*	*	*
Brain MRI	×					×
Conditional cash allocation, as appropriate based on assigned arm		×	×	×	×	×
Vitality status assessment			×	×	×	×

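### The between-arm seizure-freedom test (Hypothesis 1c) is unadjusted although baseline monthly seizure frequency is already collected: valid, but it gives up a modest amount of free precision

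*Protocol article*

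**What the plan says.** Section 6 (Statistical methods) fixes the between-arm comparison for seizure freedom: "we will use a two‐sample proportion test for the null hypothesis that the percentage of seizure freedom in the conditional cash arm". The null, as the sentence goes on to say, is that cash does no better than free medication. It attaches no covariate. By contrast, the retention comparison earlier in Section 6 is said to control for medication type.

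The next paragraph of Section 6 plans a generalized linear mixed model for the day 90, 180, 270 and 360 data, with "multiple baseline variables (e.g., including the intervention options, education level, medication status, ASM type, distance to the study clinics". This list is introduced as an example. It does not name baseline seizure frequency. The paragraph does not say which outcome is modelled or whether the model bears on the 1c conclusion.

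Seizure freedom is listed among the secondary outcomes in Section 3.3 ("Percent of PWE who achieve seizure freedom") and is also one of the three parts of the first aim (Section 1.2). The Introduction states that "seizure freedom (step four) is the outcome most valued by PWE".

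Baseline frequency is available. The other secondary outcome is "The percentage decrease in number of monthly seizures from baseline to the study endpoint of 360 days", which cannot be computed without a baseline monthly count. Table 3 marks the seizure diary at baseline, and Section 3.4 adds: "The baseline visit will include a neurologist's description of seizure history".

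**The concern.** A participant's seizure frequency before treatment is a natural candidate predictor of whether they become seizure-free. With 100 per arm, a chance imbalance in a predictive baseline variable enters the raw difference in proportions as noise. Adjusting for a value fixed before randomisation can remove part of that noise, and standardising the result keeps the same target, the marginal risk difference.

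The plan uses baseline frequency for one seizure outcome and not for the other. The sample size rests on retention only (Hypothesis 1a), so the article states no power for seizure freedom. Precision that needs no extra data is most useful where power was not planned.

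**Working it through.** **Inputs from the article.** 200 participants at 1:1, so 100 per arm. Hypothesised seizure freedom 65% (Section 1.2). Sample size based on Hypothesis 1a: 80% power and a Bonferroni-corrected familywise error of 0.05 over two tests. No alpha, power or arm difference is stated for 1c. No correlation between baseline frequency and seizure freedom is given. Table 1 gives only a mean (2.8 seizures in the past month in adults), with no SD.

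**1. The plan's own figures.** With one-sided 0.025 per test:
- One-sample: n = 0.9 × 0.1 × (1.960 + 0.842)² / 0.085² = 97.8, rounded up to 98, as stated.
- Two-sample: n = 2 × 0.9 × 0.1 × (1.960 + 0.842)² / 0.12² = 98.1, rounded up to 99, as stated.

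Both reproduce. Neither depends on the 1c test.

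**2. Unadjusted precision for 1c.** At 65% in both arms, SE = √(2 × 0.65 × 0.35 / 100) = 0.0675, a 95% half-width of 13.2 points. To show power a difference must be assumed; I take 65% v 80%. Then SE = √((0.2275 + 0.16)/100) = 0.0622 and 0.15/SE = 2.410. Power is Φ(2.410 − 1.645) = 77.8% at one-sided 0.05 and Φ(2.410 − 1.960) = 67.4% at one-sided 0.025.

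**3. Variance after adjustment.** To first order, variance is multiplied by (1 − R²), where R is the baseline-outcome correlation. At 100 per arm the simulated gain is slightly smaller. The table gives the variance ratio (adjusted over unadjusted) for a risk difference standardised from a logistic model, over 4,000 simulated trials per setting, with an assumed odds ratio per SD of log baseline frequency.

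| Assumed OR per SD | R² | Correlation √R² | Variance ratio, 65% v 65% | Variance ratio, 65% v 80% |
|---|---|---|---|---|
| 1.25 | 0.011 | 0.10 | 1.00 | 0.996 |
| 1.5 | 0.035 | 0.19 | 0.97 | 0.985 |
| 2 | 0.092 | 0.30 | 0.92 | 0.929 |
| 2.5 | 0.144 | 0.38 | 0.85 | 0.882 |

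**4. Power after adjustment, 65% v 80%.** Power = Φ(2.410/√ratio − z), using the last column.

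| Correlation | One-sided 0.05 | Gain | One-sided 0.025 | Gain |
|---|---|---|---|---|
| 0.19 | 78.3% | 0.5 points | 68.0% | 0.7 points |
| 0.30 | 80.4% | 2.6 points | 70.5% | 3.2 points |
| 0.38 | 82.1% | 4.4 points | 72.8% | 5.4 points |

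A separate simulation used an assumed lognormal baseline rate, a linear adjusted risk difference and HC3 standard errors (3,000 trials, one-sided 0.05). It gave 80.0 to 80.9%, 79.4 to 81.4% and 80.5 to 84.1% at correlations of 0.18, 0.28 and 0.38: gains of 0.9, 2.0 and 3.6 points.

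**5. Type I error.** In that simulation the adjusted test rejected a true null 5.1%, 5.1% and 4.4% of the time at nominal 5%. A simulation of the standardised logistic estimator also stayed at about 5%.

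**6. Equal arms.** If both arms are truly at 65%, the numerator is zero and rejection stays at alpha (2.5% at one-sided 0.025), adjusted or not.

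**The case against.** The strongest reply is that nothing here is wrong. A two-sample proportion test is valid under randomisation, the outcome is secondary, no stated sample size depends on it, and a condensed article may leave covariates to the analysis plan. All of that stands, except that the article does not leave the 1c test open: it names the test.

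A second reply is that adjustment is already planned through the mixed model. This stands in part. The covariate list is only an example, so a reader might infer that baseline seizure frequency is excluded, and the text does not support that. But with no named outcome and no stated role for 1c, the model cannot be taken as the adjusted 1c comparison.

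A third reply is that the gain may be close to zero. This also stands. A reader might infer that baseline frequency must vary widely, because entry requires only that a person "experienced two or more recurrent, unprovoked seizures in the past year" while adults in the earlier cohort averaged 2.8 in a month. Neither figure measures spread. In addition, 65% of those adults were taking ASMs, whereas trial entrants must have taken no daily ASM for 30 days or more. The entry criterion also sets a threshold and does not guarantee a recorded past-year count. The monthly baseline needed for the seizure-reduction outcome is the sounder source.

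**Conclusion.** The point holds as an efficiency improvement of low severity. The 1c test is valid but leaves unused a baseline measurement that the trial already collects. For assumed correlations of about 0.15 to 0.4, adjustment is worth roughly 0 to 5 points of power and about 0 to 15% less variance at 100 per arm, with type I error unchanged. The correlation, the arm difference and the alpha are all assumptions, because the article gives none of them for 1c.

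Two stronger readings are not supported. First, a gain of 6 to 9 points: the (1 − R²) formula gives 85.7% and 89.0% power from an 80% start at correlations of 0.4 and 0.5 (one-sided 0.05, 15.4-point difference), but nothing in the article supports correlations that high, and the simulated gains fall somewhat below the formula. Second, that adjustment would rescue Hypothesis 1c: the null is framed for superiority of cash, and equal arms reject only at alpha with or without a covariate.

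**What to change.** - Make the 1c between-arm estimate a risk difference standardised over all participants from a logistic model with arm and log baseline monthly seizure frequency, with a robust standard error and the same alpha as now intended. Specify how a zero count is handled, for example log(count + 1), since a person can qualify on two seizures in a year and have none in the last month.
- Keep the raw two-sample proportion test as a sensitivity analysis.
- Include the same baseline term in any longitudinal seizure model, and state which outcome the mixed model serves and how it relates to 1c. Its present examples are "including the intervention options, education level, medication status, ASM type, distance to the study clinics". ASM type may be chosen after randomisation and should not enter the adjusted 1c estimate unless it is fixed beforehand.

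The cost is a paragraph of analysis-plan wording and a few lines of code, with no new data. Baseline frequency may be partly recalled; this reduces the gain but does not bias the arm comparison. The choice should be fixed before outcome data are seen.
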